## Methods

3

### Study design

3.1

This is a prospective patient cohort registry (NCT03297827). Six hundred patients with the diagnosis of AS (IS and HS) will be recruited over the period of 3 years (2018–2021). The overview of the study design is presented in Figure 1. Plasma samples will be collected on admission and after 24 h. Plasma ILs (1, 4, 6, 10, 17, 23, 33, 36, and 37), platelet-derived growth factor (PDGF), vascular endothelial growth factor (VEGFM), tumor necrosis factor (TNF-a), ANNULIN, matrix metallopeptidase (MMP) 9 and 12, nuclear factor kappa-light-chain-enhancer of activated B cells **(**NFk-B), myeloperoxidase (MPO), glia-maturation factor (GMF), SI00 calcium-binding protein B (S100B), and GM6001 will be measured using enzyme-linked immunosorbent assay (ELISA).

**Figure 1 F1:**
[figure not shown]
Schematic representation of the CRISP study trial.

### Eligibility criteria

3.2

Inclusion criteria:

1.All stroke patients (hemorrhagic and ischemic) presenting within 24 h of onset based on clinical and radiographic examination2.Adult male/female patients ages >18 years old

Exclusion Criteria:

1.History of prior stroke or any other neurodegenerative or neuroinflammatory disease (Dementia of Alzheimer's type, Parkinson's disease, multiple sclerosis, etc) and acute infectious diseases (respiratory tract infections, urinary tract infections, etc).2.Patients with chronic inflammatory systemic illness (including premorbid diagnosis of rheumatoid arthritis, systemic lupus erythematosus, sarcoidosis or other immune-mediated diseases)3.Individuals ages <18 years4.Pregnant women5.Prisoners6.Low likelihood of survival >24 h, based on clinical assessment (mRS ≥ 5)

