## Abstract

Inflammation is an important pathophysiological process after an acute stroke (AS). Pro- and anti-inflammatory molecules (cytokines and interleukins) are the key players during this mechanism. Emerging evidence indicate that these molecules can serve as biomarkers of stroke progression and outcome and as novel therapeutics agents. The aim of this study is to explore the temporal changes in these molecules and validate them as biomarker of AS progression and neurological outcome.

The “Cytokine Registry In Stroke Patients (CRISP)” is a prospective cohort study of 600 AS patients presenting to the tertiary hospital with-in 24 h of the onset of symptoms. Plasma cytokines and interleukins will be collected at admission and 24 h after and will be measured using enzyme-linked immunosorbent assay (ELISA) to evaluate the difference in their variation among different gender, race and ethnicity and their association with various neurological outcomes. The primary exposures are biological sex (male, female) and race/ethnicity. Confounding variables include age, vascular risk factors, infarct size, stroke onset to presentation time, and identified stroke etiologies. Matched controls will be used for the comparison and evaluation of the difference among gender and race/ethnicities.

CRISP is a prospective observational study that investigates the role and relationship of molecular biomarkers identifying specific and relevant targets pertinent for monitoring the progression and outcome in AS patients.

Trial Registration: The study is registered on ClinicalTrial.gov: https://clinicaltrials.gov/ (NCT03297827).

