### Data Collection

3.3

Patients who will meet all inclusion criteria/exclusion criteria will be consented. Two sets of plasma samples will be obtained from individual participants; one upon admission to the hospital, and the second sample 24 h apart from the first one. Both sets of blood samples (3–5 mL) will be collected from peripheral veins according to the routine puncture method as standard of care. After centrifugation, the resulting plasma supernatants will be stored at −80°C. The samples will be transported and handled according to the federal guidelines. Additional hospital data will be collected by chart review. This includes last known well or the time of onset of symptoms (according to patient or bystander), the presence of any neurological deficit or hemiparesis (if applicable), demographics, vital functions, neurological examination (NIHSS), imaging include non-contrast CT scan, CT angiography (CTA), digital subtraction angiography (DSA), and/or CT perfusion, clinical data including medical history, comorbidities, medication use, laboratory results, and physical examination will be collected using the chart review. Information regarding the corresponding treatment including door to needle time and door to groin time will be also collected. Other parameters like length of hospital stay, discharge location, and modifies Rankin Scale (mRS) at 3 months will be collected as part of the protocol. All paper consents will be secured in the locked cabinet in the principal investigator (PI) office. The PI's research team will be responsible for consenting, collecting samples, storage in secure refrigerator, running the assays and entering the inferences and other clinical details into a secure REDCap database.^[22]^ REDCap (Research Electronic Data Capture) is a secure, web-based application designed to support data capture for research studies, providing

1.an intuitive interface for validated data entry;2.audit trails for tracking data manipulation and export procedures;3.automated export procedures for seamless data downloads to common statistical packages; and4.procedures for importing data from external sources.

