### Study outcomes

3.4

The primary objective of this study is to measure the levels of the reported cytokines and other analytes that have a continuous measure, from the plasma of AS patients using standardized ELISA kits. The primary exposures are biological sex (male, female) and race/ethnicity (American Indian/Alaskan Native, Asian/Pacific Islander, African American, Whites, and Hispanics). Confounding variables to adjust for are age, vascular risk factors, medications (anti-inflammatory), infarct size, stroke onset to presentation time, and identified stroke etiologies (based on TOAST criteria).

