### Recruitment

3.5

This study will be performed at the tertiary care hospital. It will be conducted in accordance with the principles of Good Clinical Practice (GCP). The study protocol was approved by the Institutional Review Board (IRB). Study participants will be recruited through the department of Neurology after the written informed consent. Informed consent can be very challenging in AS patients. Patients may suffer from language deficit and/or other cognitive impairment that can hamper the informed consent procedure. The primary stroke team and/or the physician provider will assess the mental competence of the potential study participant to determine whether they are capable of giving informed consent. Hence, if the patient is ineligible the study will include the legal authorized representative (LAR) as part of the informed consent process. A study team member will obtain both verbal and written consent and will explain the study protocol to the potential participants. All the patients with the diagnosis of AS will be approached for the consent procedure. In addition, a flyer detailing an overview of the study protocol, as well as a copy of the formal consent form, will be given to potential trial participants. After obtaining the informed consent, the study team member will assign a unique study identification number (SIN) and enter the information in the REDCap database. After informed consent, a pre-randomization assessment for every recruiting patient will be done, evaluating their medical records for any autoimmune and/or inflammatory disorders.

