### Data analysis and sample size

3.6

The study team along with the core statistical division will evaluate all the study trial outcomes. One Way Analysis of Covariance (ANCOVA) will be employed, followed by post hoc tests while adjusting for multiple comparisons using the Sidak adjustment. As a secondary analysis, we will also look at the correlation network of these cytokines after stratification by sex and race/ethnicity. According to the ANCOVA model, based on 80% power and 5% significance level, the minimum sample size is 420 AS participants. The primary exposures are biological sex (male, female) and race/ethicity (American Indian/Alaskan Native, Asian/Pacific Islander, African American, Whites, and Hispanics). Confounding variables adjusted in the model include age, vascular risk factors, infarct size, and identified stroke etiologies. Matched controls will be used for the comparison and evaluation of the difference among age, gender, and race/ethnicities.

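### The only timing confounder named runs from stroke onset to presentation, not to the blood draw, and the ANCOVA covariate list has no timing term

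*Protocol article*

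**What the plan says.** All references are to the protocol article.

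- **Window.** Section 3.2 includes "All stroke patients (hemorrhagic and ischemic) presenting within 24 h of onset based on clinical and radiographic examination". The Abstract words it the same way: "presenting to the tertiary hospital with-in 24 h of the onset of symptoms". Both end at arrival.
- **Timing confounder.** Section 3.4 lists, among the variables to adjust for, "infarct size, stroke onset to presentation time, and identified stroke etiologies". The Abstract also lists the onset-to-presentation interval. No other timing variable is named.
- **Analysis model.** Section 3.6 states: "Confounding variables adjusted in the model include age, vascular risk factors, infarct size, and identified stroke etiologies". Time does not appear.
- **Draws.** Sections 3.1 and 3.3 place the first draw at admission. Section 3.3 places the second 24 h after the first.
- **Consent.** Section 3.3 opens with "Patients who will meet all inclusion criteria/exclusion criteria will be consented" and then describes sampling. Section 3.5 says that consent can be hard to obtain in acute stroke, requires a capacity assessment, and adds that "if the patient is ineligible the study will include the legal authorized representative (LAR) as part of the informed consent process".
- **Start of the clock.** The chart-review list in section 3.3 collects "last known well or the time of onset of symptoms (according to patient or bystander". No rule says which of the two is used.

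**The concern.** The first objective in section 2 is the concentration and time course of the cytokines. If a level changes over the first hours after stroke, the relevant time is from onset to the draw. Section 3.4 adjusts for a shorter interval. An analyst who followed it to the letter would leave the time between arrival and draw in the outcome.

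That remainder need not be random. By the article's own account, consent is harder in patients with impaired language or cognition, and these deficits go with stroke severity, which the primary hypothesis concerns. A later draw in more severe patients could then look like a severity effect on the level. The same would hold for sex or race/ethnicity groups if their delays differed, but the article gives no evidence that they do.

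The covariate list in section 3.6 adds to this. Read as it stands, the model adjusts for no timing at all.

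**Working it through.** The plan has no figure to reproduce here: 24 h is a design limit, and the minimum sample size of 420 does not bear on the point.

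**Inputs from the article.** P, onset to presentation, is at most 24 h (3.2). Draw 1 is nominally at admission, and draw 2 is 24 h after draw 1 (3.1, 3.3). The named timing covariate is P (Abstract, 3.4). The model list has no timing covariate (3.6).

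**Assumptions, not in the article.** P is uniform on 0 to 24 h. D, presentation to draw 1, is exponential with mean m and independent of P. Values of m from 1 to 12 h are shown to cover a range.

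**Step 1: what the covariate misses.** Onset to draw 1 is T = P + D. Adjusting for P leaves D. With Var(P) = 24²/12 = 48 and Var(D) = m², the share of Var(T) left unadjusted is m² / (48 + m²).

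| Mean delay m (assumed) | Calculation | Share of Var(T) left after adjusting for P |
|---|---|---|
| 1 h | 1/49 | 2% |
| 3 h | 9/57 | 16% |
| 6 h | 36/84 | 43% |
| 12 h | 144/192 | 75% |

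A simulation under the same assumptions gave 2.0%, 15.8%, 43.2% and 75.2%.

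**Step 2: the section 3.6 list.** With no timing term, all of Var(T) is unadjusted. At m = 1 h, adding P would already account for 48/49, or 98%. If draws are prompt, the missing timing term therefore matters more than which interval is used. If draws are late, both matter.

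**Step 3: what this does to levels.** These shares describe sampling time, not bias in a cytokine. The bias in a comparison of levels is (slope per hour) × (difference in mean D between groups). The article gives neither quantity, so no bias figure can be derived from it.

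**Step 4: within-patient change.** Write the level as a + b·t. Draw 1 is at P + D and draw 2 at P + D + 24, so the change is 24b and D cancels. A common shift in draw time affects levels. It affects change only if the time course is not linear.

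**Step 5: the start of the clock.** Last known well cannot be later than true onset, so it can only lengthen the recorded interval. Assuming that 10% to 30% of patients have a gap between last known well and onset averaging 4 to 8 h, the simulated reliability slope of recorded on true onset-to-arrival time was 0.98 to 0.91. That is modest noise in the covariate.

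**The case against.** The strongest reply is that the article places draw 1 at admission, so presentation and draw nearly coincide. No sentence says that the draw is held until consent; that is an inference from the order of steps in sections 3.3 and 3.5. The exclusion of patients with mRS of 5 or more also removes some of those most likely to need a representative. Collection tolerances and time stamps are details that a journal article may leave to the full protocol. All of this stands. It limits the size of the problem, and missing tolerances are not the point here. The point rests on what the article does fix: the interval named as a confounder, and a model list without any.

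Three stronger readings are tempting and are not supported.

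- A reader might infer that the first sample has no bounded time from onset. The schedule gives it a nominal anchor at admission, and it drifts only as far as practice departs from that.
- A reader might infer that the choice between last known well and onset makes eligibility ambiguous. The window is worded from onset in both places, and last known well can only tighten it. Only if time of discovery were recorded as onset would the limit loosen, and no section says that it is.
- A reader might infer a large false-positive rate. With 300 against 300 patients (standard error √(2/300) = 0.0816 SD), a 3 h difference in delay and a slope of 0.05 SD per hour give a shift of 0.15 SD and about 45% rejection. At 0.02 SD per hour, the same delay gives 0.06 SD and about 11%. Every one of these delays and slopes is assumed.

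The word used in section 3.6 to introduce the covariates may also mean that the list is not complete. Even so, it differs from section 3.4, and the two need reconciling.

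**Conclusion.** The point holds in a limited form. Section 3.4 names an interval that is not the age of the sample, and section 3.6 lists no timing variable. Any delay from presentation to draw is therefore unadjusted in between-group and severity comparisons of cytokine levels. Within-patient change over 24 h is protected if the time course is roughly linear.

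The effect is small if draws really happen at admission (about 2% of onset-to-draw variance at an assumed mean delay of 1 h) and grows if consent holds them back (16% to 43% at 3 to 6 h). These shares rest on a uniform arrival time and an exponential delay independent of it. The unfixed start-time rule is a secondary matter of covariate accuracy. The change is worth making because it costs little, and a draw time that was never recorded may not be recoverable.

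**What to change.** - **Section 3.4:** replace onset-to-presentation time by onset-to-draw time, calculated for each sample.
- **Section 3.6:** add that variable to the ANCOVA covariates, so that the lists in 3.4 and 3.6 agree on timing.
- **Section 3.3:** record the clock time of each draw and whether onset was witnessed. State one start-time rule: witnessed onset where there is one, last known well otherwise.
- **Sensitivity analysis:** repeat the comparisons of levels in patients with witnessed onset.

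The cost is a few time fields and slightly more analysis. The 24-h eligibility window need not change, so no patients are lost.

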### Data Collection

3.3

Patients who will meet all inclusion criteria/exclusion criteria will be consented. Two sets of plasma samples will be obtained from individual participants; one upon admission to the hospital, and the second sample 24 h apart from the first one. Both sets of blood samples (3–5 mL) will be collected from peripheral veins according to the routine puncture method as standard of care. After centrifugation, the resulting plasma supernatants will be stored at −80°C. The samples will be transported and handled according to the federal guidelines. Additional hospital data will be collected by chart review. This includes last known well or the time of onset of symptoms (according to patient or bystander), the presence of any neurological deficit or hemiparesis (if applicable), demographics, vital functions, neurological examination (NIHSS), imaging include non-contrast CT scan, CT angiography (CTA), digital subtraction angiography (DSA), and/or CT perfusion, clinical data including medical history, comorbidities, medication use, laboratory results, and physical examination will be collected using the chart review. Information regarding the corresponding treatment including door to needle time and door to groin time will be also collected. Other parameters like length of hospital stay, discharge location, and modifies Rankin Scale (mRS) at 3 months will be collected as part of the protocol. All paper consents will be secured in the locked cabinet in the principal investigator (PI) office. The PI's research team will be responsible for consenting, collecting samples, storage in secure refrigerator, running the assays and entering the inferences and other clinical details into a secure REDCap database.^[22]^ REDCap (Research Electronic Data Capture) is a secure, web-based application designed to support data capture for research studies, providing

1.an intuitive interface for validated data entry;2.audit trails for tracking data manipulation and export procedures;3.automated export procedures for seamless data downloads to common statistical packages; and4.procedures for importing data from external sources.

### Study outcomes

3.4

The primary objective of this study is to measure the levels of the reported cytokines and other analytes that have a continuous measure, from the plasma of AS patients using standardized ELISA kits. The primary exposures are biological sex (male, female) and race/ethnicity (American Indian/Alaskan Native, Asian/Pacific Islander, African American, Whites, and Hispanics). Confounding variables to adjust for are age, vascular risk factors, medications (anti-inflammatory), infarct size, stroke onset to presentation time, and identified stroke etiologies (based on TOAST criteria).

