## Introduction

1

Stroke is a neurologic deficit occurring due to interruption of cerebral blood flow or from bleeding by a ruptured blood vessel in the brain.^[1,2]^ According to World Health Organization (WHO), it is the second leading cause of deaths worldwide.^[3]^ In the United States (US), it is the fifth leading cause of mortality killing around 140,000 Americans each year and the leading cause of morbidity and complex disability.^[4,5]^

During acute stroke (AS), the deprivation of oxygen, glucose, and other nutrients to the brain causes dysfunction of the neurovascular unit. Additionally, the breakdown of the blood–brain barrier, and induction of the inflammatory cascade results in subsequent brain damage.^[6,7]^ This is characterized by an increase in multiple pro-inflammatory and decrease in anti-inflammatory cytokines, which also correlates with progression of stroke injury.^[6,8]^ Various pro-inflammatory cytokines are observed in experimental models and in stroke patients that may correlate with infarct size and stroke outcomes.^[9–14]^ Cytokines and interleukins including TNF-α, interleukin (IL)-1, IL-6, and IL-10, have been studied as therapeutic and prognostic markers in AS.^[10,12,15,16]^ IL-10 is an anti-inflammatory molecule, observed to be associated with negative feedback, whereas IL-6 and TNF-α are reported to be increase in both ischemic and hemorrhagic stroke patients.^[11,16,17]^ Moreover, glial cell markers such as S100B and various other cytokines have also been reported to be associated with infarct size, neurological outcome, and prognosis among these patients.^[10,17–21]^

The inflammatory mechanism and the interaction between the pro- and anti-inflammatory cytokines in AS patients is still ambiguous. Although, studies have indicated changes in systemic cytokine profile in response to experimental stroke, few studies have assessed peripheral cytokine levels in human stroke patients and their association with the neurological outcome.^[10]^ As such, for the use of cytokines as potential biomarkers and prognosis of stroke, it is important to design clinical stroke studies on peripheral cytokine expression that focuses on the temporal profile, comorbidities, and demography.

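### The single ANCOVA adjusts for infarct size and TOAST etiology, but the cohort includes hemorrhagic stroke, for which neither covariate has a valid value, and no stroke-type term is listed

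*Protocol article*

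**What the plan says.** **Population.** Study design (3.1): "Six hundred patients with the diagnosis of AS (IS and HS) will be recruited". Eligibility criteria (3.2): "All stroke patients (hemorrhagic and ischemic) presenting within 24 h of onset". The Introduction defines stroke to match, as interrupted flow or a deficit "from bleeding by a ruptured blood vessel in the brain".

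**Covariates.** Study outcomes (3.4) lists the variables to adjust for, among them infarct size and "identified stroke etiologies (based on TOAST criteria". Data analysis and sample size (3.6) puts most of that list into the model: "Confounding variables adjusted in the model include age, vascular risk factors, infarct size, and identified stroke etiologies".

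**Model and size.** Section 3.6: "One Way Analysis of Covariance (ANCOVA) will be employed, followed by post hoc tests", with a Sidak adjustment, and "based on 80% power and 5% significance level, the minimum sample size is 420 AS participants".

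Nowhere does the article give a stroke-type term, a hematoma counterpart to infarct size, a hemorrhagic etiology class, an analysis split by stroke type, or a restriction of these two covariates to ischemic patients.

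**The concern.** A least-squares model needs a usable value of every covariate for every patient. Infarct size has no meaning for a primary hemorrhage, and TOAST has no class for one. So two covariates named for the main model cannot be filled in for a group that the protocol enrols on purpose.

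What is at stake is what the sex and race/ethnicity contrasts describe. If hemorrhagic patients are left out, the contrasts are about ischemic stroke but carry the label of acute stroke. If they are kept by entering an infarct size of 0 and a residual TOAST class, a hemorrhage is treated as the smallest possible infarct of undetermined or other cause. The infarct slope and the etiology effect then absorb part of the difference between stroke types. Were the hemorrhagic share also to differ by sex or race/ethnicity, some of that difference would pass into the primary contrasts. The article gives no figures on this.

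**Working it through.** **1. Population against covariates**

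| Element | Ischemic stroke | Primary hemorrhage |
|---|---|---|
| Eligible (3.2), counted in the 600 (3.1) | yes | yes |
| Infarct size (3.4 and 3.6) | defined | not defined |
| Etiology by TOAST (3.4) | defined | no class |
| Stroke-type term (3.4, 3.6) | none listed | none listed |

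The infarct-size row is enough by itself: the covariate is named in both sections, and its meaning needs no outside source. The TOAST row relies on the common understanding that TOAST classifies ischemic stroke, which the article does not spell out.

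**2. The plan's own figure**

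The 420 (80% power, 5% significance) cannot be reproduced, because the article gives no effect size, covariate R² or group split. It can be back-solved from the noncentral F distribution, with noncentrality f²·N and denominator df = N − groups − covariates. With 6 covariates assumed, N = 420 gives 80% power at Cohen's f of about:
- 0.137 for two sex groups
- 0.170 for five race/ethnicity groups
- 0.195 for ten sex-by-race/ethnicity cells

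Taking 4 or 10 covariates leaves these values unchanged to three decimals.

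**3. Loss if hemorrhagic patients are excluded**

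Inputs: 600 planned (3.1) and 420 minimum (3.6). The hemorrhagic share h is not in the article, so 10-30% is assumed, with 40% shown to mark the crossover. Remaining N = enrolled × (1 − h). Power is computed at the three f values above.

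| h | Left of 600 | Power | Left of 420 | Power |
|---|---|---|---|---|
| 10% | 540 | 0.89-0.91 | 378 | 0.75-0.76 |
| 20% | 480 | 0.85-0.86 | 336 | 0.68-0.71 |
| 30% | 420 | 0.80 | 294 | 0.61-0.65 |
| 40% | 360 | 0.72-0.74 | 252 | 0.52-0.58 |

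Break-even share at full enrolment: 1 − 420/600 = 0.30.

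At the planned 600, the minimum is therefore met for any share up to 30%. Below that share the harm is the absence of the hemorrhagic group, not a shortage of patients overall. If recruitment stops near 420, any exclusion takes the analysed number below the minimum.

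**The case against.** **Handling is not stated.** This is a condensed article, and a statistical analysis plan may say how inapplicable covariates are coded or split the model by stroke type. That stands to this extent: neither exclusion nor mis-coding is announced, and both are inferred from the model as listed. It does not remove the point, because the article itself names the population, the model and the covariates, and these do not fit together. A later plan could resolve this only by changing what Sections 3.4 and 3.6 state.

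**Etiology could include hemorrhage.** Section 3.6 does not repeat TOAST. If the etiology factor had a hemorrhage level, those patients would have their own intercept, a constant infarct size for them would do no harm, and the infarct slope would come from ischemic patients. This is correct, and it is close to the fix. But Section 3.4 ties the term to TOAST, so the text points the other way.

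**The sample size survives.** A reader might infer that the analysis must fall short of 420. The article does not support that: 600 are planned, and the shortfall needs a share above 30% or early closure of recruitment.

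**Infarct size as a consequence of inflammation.** The Introduction says "induction of the inflammatory cascade results in subsequent brain damage", so a reader might infer that adjusting for infarct size biases the sex and race/ethnicity contrasts. The same section also describes ischemia setting off the cascade, and cytokines that may merely correlate with infarct size. It fixes no single causal direction and gives no slope. Infarct size may be a legitimate severity adjustment, and whether to condition on it is a choice of target quantity. That claim is not made here.

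**Conclusion.** The stated model is wrong as written for the stated population. Infarct size and TOAST etiology have no valid value for primary hemorrhage, and nothing in Sections 3.4 or 3.6 separates the stroke types. The result would either be an ischemic-stroke result under a broader label or rest on arbitrary codes.

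The number of patients affected cannot be read from the article. At an assumed hemorrhagic share of 10-30%, it is 60-180 of 600, leaving 540-420. Falling below 420 is conditional: it needs a share above 30%, or enrolment that ends near 420 (378-294 left at the same shares). The power figures rest further on effect sizes back-solved from the 420, not on any that the protocol gives. Certain dropout, a certain shortfall and biased sex or race/ethnicity contrasts from infarct adjustment are stronger readings that the article does not establish.

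**What to change.** In Sections 3.4 and 3.6:

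- Add stroke type (ischemic or hemorrhagic) as a factor, or analyse the two types in separate strata.
- Replace infarct size by lesion volume within type: infarct volume for ischemic stroke and hematoma volume for hemorrhagic stroke, each with its own slope.
- Apply TOAST only within ischemic stroke, with hemorrhage as a separate level of the etiology factor. In a single model that level is itself the stroke-type indicator, so it should enter once.
- State whether the 420 refers to all acute stroke or to ischemic stroke only.

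A sex and race/ethnicity model without infarct size may be shown as a sensitivity analysis. It need not replace the adjusted model.

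**Cost.** The wording of two sections changes, and hematoma volume has to be read from the non-contrast CT that Section 3.3 already collects. A single model gains about two parameters (one for stroke type, one for the hematoma slope), which is negligible against 420 or 600. Separate strata cost more precision, because every covariate effect is then estimated within type.
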